**Methods:**

The RCT is being conducted in 7 sites across Australia. We aim to recruit 300 families to the study: 150 control (services as usual) and 150 intervention (services as usual + volunteer home visiting) families. Intervention families will receive the service for 3-12 months according to their needs, and all participants will complete 6 data collection points over 15 months. A minimum of 80 volunteers will also be recruited, along with a matched community comparison group. The volunteers will complete 3 data collection points over 12 months. Primary outcomes include community connectedness and parenting competence. Secondary outcomes include parent physical and mental health; general parent well-being; parent empowerment; the child-parent relationship; sustainability of family routines; child immunization; child nutrition or breastfeeding; number of accidental injury reports; and volunteer health, well-being, and community connectedness.

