### Hypothesis

Families receiving a volunteer home visiting service intervention will have significantly better family outcomes at 15 months post program entry (higher sense of parenting competence and stronger community support networks) than those allocated to continue to receive usual community-based support services.

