**Primary Outcomes**									
	Community connectedness		✓	✓	✓	✓	✓	✓	Community Connectedness Scale [37]; Social Provisions Scale [38].
	Parenting competence		✓	✓	✓	✓	✓	✓	Parenting Sense of Competence Scale [39].

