### Data Analysis

#### Quantitative Analysis

Primary and secondary outcomes will be extracted and analyses conducted using SPSS Version 25.0. Analysis will be completed both on an intention-to-treat and a per-protocol basis. Families will be considered to have received the scheduled dose if they receive visits from the volunteer for at least 3 months with no gap between visits of more than 2 weeks. Volunteer outcomes will be analyzed using cross-sectional comparative analysis. Participant demographic data will be analyzed using basic descriptive statistics. Prior to the analysis of outcome measures, data will be assessed for outliers and normality. Scale variables will be analyzed using independent *t* test or analysis of variance or their nonparametric counterparts (eg, Mann–Whitney U test) if appropriate. Mixed modeling will be completed on the primary and secondary family outcomes to assess the effect of the intervention over time while adjusting for possible confounders. Categorical variables will be analyzed using odd ratios or chi-square analysis. For all analyses, two-tailed tests will be undertaken: findings with α<0.05 will be determined to be statistically significant. ESs will be calculated for all trends (α<0.1) and statistically significant findings; (ES≈0.5 [Cohen *d*]) will be considered clinically meaningful. Overall, the program will be considered to have been effective if at least one of the primary outcomes is positive and the other is neutral.

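### The success rule contradicts itself: it asks for at least one positive primary outcome but requires the other to be neutral, which leaves out the both-positive result the hypothesis predicts

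*Protocol article*

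**What the plan says.** The Abstract (Methods) names two primary outcomes: "Primary outcomes include community connectedness and parenting competence". Table 1 lists the same two constructs.

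The Hypothesis section predicts that intervention families will do significantly better than usual-care families at 15 months on both: "higher sense of parenting competence and stronger community support networks".

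The Quantitative Analysis section sets the test level, "For all analyses, two-tailed tests will be undertaken: findings with α<0.05 will be determined to be statistically significant", and closes with the only rule in the article that turns the primary results into an overall verdict. Under it the program counts as "effective if at least one of the primary outcomes is positive and the other is neutral".

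**The concern.** With two primary outcomes, the two halves of the rule do not fit together. *At least one* ordinarily means one or both. The second condition, joined by *and*, requires the other outcome to be neutral. If both are positive, no other outcome is left to be neutral, and the condition as written is not met. To satisfy both halves literally, *at least one* has to shrink to *exactly one*.

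The case left out is the best result the trial could have, and the one its hypothesis predicts. A pre-specified rule should give the verdict for that case directly, without needing to be interpreted once results are known.

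**Working it through.** **Step 1. Set the rule against every pattern of results.** Each primary outcome can be positive (significantly better), neutral (no significant difference) or negative (significantly worse). This takes positive and neutral to refer to the two-sided 0.05 test; the rule itself does not say so.

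| Outcome A | Outcome B | At least one positive? | Other neutral? | Literal rule met? | Evident intent met? |
|---|---|---|---|---|---|
| positive | positive | yes | no | **no** | **yes** |
| positive | neutral | yes | yes | yes | yes |
| positive | negative | yes | no | no | no |
| neutral | neutral | no | – | no | no |
| neutral | negative | no | – | no | no |
| negative | negative | no | – | no | no |

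The literal text and the evident intent differ in one row only: both positive, the row the Hypothesis section predicts.

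**Step 2. How likely is that row? (illustration)**

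Inputs from the article: 100 families per group analyzed and an effect size of 0.5 (Sample Size); two-sided α = 0.05 for each test (Quantitative Analysis). Assumptions: the same true effect d on both primary outcomes, and a correlation r between the two test statistics of 0 to 0.7. The article gives no value for r.

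Power per outcome:
- Mean of the z statistic = d × √(n/2) = 0.5 × √50 = 3.536.
- Power = Φ(3.536 − 1.960) = Φ(1.576) = 0.942 (noncentral t: 0.940).

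The Sample Size section states power of 0.80 for effects of 0.5 or larger with 100 per group. That figure is not reproduced exactly; it is true as *at least 0.80*. Power of exactly 0.80 with 100 per group corresponds to d = (1.960 + 0.842) × √(2/100) = 0.396. Both values of d are used below.

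By hand for d = 0.5 and r = 0:
- Both positive: 0.942² = 0.888.
- Exactly one positive: 2 × 0.9424 × 0.0576 ≈ 0.108.
- At least one positive: 1 − 0.0576² = 0.997.

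For the other rows, 4 million pairs of correlated normal test statistics were simulated:

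| True d on both | r | Both positive | Literal rule met | Reworded rule met |
|---|---|---|---|---|
| 0.5 | 0 | 0.888 | 0.108 | 0.997 |
| 0.5 | 0.3 | 0.894 | 0.097 | 0.991 |
| 0.5 | 0.5 | 0.900 | 0.086 | 0.985 |
| 0.5 | 0.7 | 0.908 | 0.068 | 0.977 |
| 0.396 | 0 | 0.640 | 0.320 | 0.960 |
| 0.396 | 0.7 | 0.712 | 0.174 | 0.887 |
| 0 | 0 | 0.001 | 0.047 | 0.048 |
| 0 | 0.7 | 0.008 | 0.034 | 0.042 |

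The reworded rule is at least one positive and none negative, that is, the sum of the two columns before it. With no effect on either outcome, the two versions differ by less than 0.01, so the correction barely changes the chance of a false declaration of success.

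**The case against.** The strongest reply is that no reader would be misled. *At least one* already signals that two positives should count, since the phrase would be pointless otherwise. The primary research question and the hypothesis both name the two outcomes together. The rule also says *if*, not *only if*: it gives a condition under which the program counts as effective and does not say that every other pattern means ineffective. All of this stands. It makes the intent clear and the practical risk low.

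Two stronger readings are tempting, and the article supports neither.

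- A reader might infer that the trial would report two positive primary outcomes as a failure, and so would succeed only about 7% to 11% of the time at d = 0.5. Those figures describe the literal text. Nothing in the article suggests the team would act that way, and the hypothesis points the other way.
- A reader might infer that the trial was sized for both outcomes being positive. The Sample Size section rests on the PSCS Satisfaction subscale and the Client Enablement Index. Parent empowerment, measured by an enablement instrument, is secondary in Table 1. The section gives no calculation for either community connectedness scale and no joint power.

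The reply does not remove the inconsistency. The sentence is stated in the article, it is the only overall decision rule there, and it gives the right verdict for the predicted result only if the reader overrides part of it.

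**Conclusion.** The point holds as a wording error in the decision rule. The two halves of the sentence conflict, and the second half omits the both-positive result that the hypothesis predicts. That conclusion follows from the text alone and needs no calculation.

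The size of the omitted case is illustrative: about 0.89 to 0.91 if both true effects are 0.5, and 0.64 to 0.71 if they are 0.396. It rests on equal effects on the two outcomes, 100 analyzed per group and an assumed correlation of 0 to 0.7. The risk to the trial's actual conclusion is low because the intended meaning can be inferred. The sentence should still be corrected, because it decides the headline verdict.

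**What to change.** Replace the sentence with: *the program will be considered effective if at least one primary outcome is significantly better (two-sided p<0.05) in the intervention group at 15 months and neither primary outcome is significantly worse; two positive outcomes satisfy this rule.*

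This resolves the conflict, ties the verdict to the significance level already stated, and uses the time point in the hypothesis. If the team meant positive in another sense, such as the effect size of about 0.5 that the same section calls clinically meaningful, the sentence should say that instead. The rewording does not settle how the two scales listed for community connectedness combine into one result; that is a separate matter.

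The cost is one sentence in the protocol and analysis plan, ideally settled before outcome results are seen. No data, participants or power are lost.

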#### Qualitative Analysis

The survey instruments include some open-ended questions. The qualitative data will be extracted into a text file for analysis and entered into NVivo (QSR International). Analysis of the open-ended responses will employ a thematic approach, with themes and relationships between themes identified and described. The first ten interviews will be dual-coded, followed by the development of a coding framework then independent coding with regular checks for inter-rater reliability. Analysis will initially focus on the family as a case and explore change in the family’s reported experience over time. It will then expand to compare themes across the families as a group to capture the collective experience.

### Ethics

Ethics approval for the study was granted by the Macquarie University Human Research Ethics Committee (Reference number: 5201401144).

### 
Data Availability

The data that support the findings of this study will be made publicly available at the conclusion of the research on request to the corresponding author RG.

## Results

Seed funding for this project was provided by a private philanthropist, who went on to fund the effectiveness trial described here commencing in 2016. Data collection is currently underway and will be complete by the end of 2018. The first results are expected to be submitted for publication early in 2019.

## Discussion

In this study, we aim to explore the effectiveness of a volunteer home visiting program designed to provide support to families with young children who might otherwise “fall between the cracks” because they are not eligible for intensive family support services but need more support than is available through universal primary services. The Volunteer Family Connect study will provide evidence of the outcomes for families based on the program logic of volunteer home visiting [1] and outcomes desired and valued by parents. This study assesses the effectiveness of volunteer home visiting on its own merits and contribution to the service landscape, rather than as a program equivalent to, or potential substitute for, professional services.

RCTs can be an uncomfortable methodological approach for not-for-profit organizations. Their employees are generally guided by an altruistic and empathic approach, rather than a rigidly scientific approach, and randomly denying support to someone they believe would benefit can be challenging. Time was spent with those delivering the program to discuss the ethical situation in the context of delivering the previously untested service that did not have evidence of effectiveness. The lengthy lead in time for this project was essential to secure support for the research across all levels of the organizations, from CEOs and board members, through to program coordinators and volunteers. Some volunteers and program coordinators did not want to be involved, and the services have also experienced some difficulties with their referral networks, with some referrers ceasing to refer families during the research trial. Understanding these significant challenges for participating organizations and their ongoing commitment to ensure a rigorous research approach is commendable. Launching this research is an indication that within the not-for-profit sector, rigorous research is feasible. It does, however, need to be embedded within trusting relationships and will need many formal and informal conversations across all levels of the organization, which can take several years.

Future research will explore different modes of program delivery, including whether volunteer home visiting can be effectively delivered using technology such as telephone and videolinks. This work will complement the existing research exploring the role of technology in providing professional and other support services to those in rural and remote regions [31].

A strength of this study is that it is part of a comprehensive program of research that employs an ecological approach [4] guided by an understanding that the health and well-being of parents, the stability of families, the strength of social interactions, the safety of neighborhoods, and respect for cultural contexts are all equally important for achieving positive outcomes for children. In conjunction with the RCT of family outcomes are the following: (1) a matched comparison study on the benefits of volunteering; (2) a mixed-methods study of program implementation that explores program quality and fidelity; and (3) a social return on investment analysis. This RCT and the three additional studies will interlink and directly inform the analysis and interpretation of findings across the program of research. As a whole, this program of research has the potential to make a significant contribution to our understanding of the support and service needs of vulnerable families and the value of volunteering as a mechanism to mobilize and strengthen communities.

## Abbreviations

ES: effect size
PRECIS: PRagmatic Explanatory Continuum Indicator Summary
RCT: randomized controlled trial
